### Data management

DMDC used information from DEERS to construct the sampling frame and transmit it to project staff at NHRC. The PII needed by NHRC to create this dataset include electronic data interchange personal numbers (EDIPNs), names, contact information and demographic data, including birthdate. Project staff at NHRC assign TWO key codes to every military parent in the sample: a "field" key code and a "data" key code. Names and contact information needed for data collection, with the field key code as an identifier, are transmitted to the data collection team for recruitment and data collection purposes. EDIPNs and all other identifiers including dates, along with the crosswalk to the data key codes, are retained and kept confidential at NHRC. Contact information along with field key codes are loaded into the data collection operations database to enable the process of recruitment, consent and data collection.

The forms needed for both types of data collection (online surveys and phone interviews) are hosted on the Qualtrics platform. Although the interview team uses these forms, they do not have back-end access to participant survey or interview responses. The only identifier in the Qualtrics data system is the field key code. In addition, none of the PII necessary for recruitment and no PHI will be transmitted to or collected via the Qualtrics system.

Identifying information and participant data never appear or be stored together. To make it possible to match new and archival data, after all data collection for each wave is complete, data sets will be sent to NHRC, merged with DoD archival records, deidentified using National Institutes of Health Guidelines, and–following destruction of the Purdue key code—distributed to investigators for analyses. Once identifiers are removed, other researchers may use the newly collected data. Due to DoD regulations, however, the archival data may not be shared.

#### Data cleaning and preliminary analyses

Prior to analyses, data will be screened for logical inconsistencies and structural problems related to filters and skip patterns, univariate and multivariate outliers, and nonnormality. Each detected problem will be corrected if possible via recoding, data transformation, set to a specific missing code, or left unchanged but flagged. Patterns of missing data will be identified and replaced using archival records where possible. We will check for **introduced bias** associated with interviewer or team, date of interview, question order (e.g., whether mothers or fathers were asked about first), or other factors. When bias is found, that variable will be controlled in subsequent analyses. New timing variables will be constructed, indexed by child age and deployment dates.

#### Psychometrics

Confirmatory factor analysis (CFA) will be used to confirm structures of multi-item measures and measurement equivalence of instruments over time [100]. Cronbach’s alpha [101] also will be calculated. Latent variables will be used when advantageous.

#### Benchmarking

Comparisons will be conducted with established norms or nationally representative community samples, matching participants based on age, sex, education, and minority status wherever possible [102]. For example, exposures to adverse experiences will be benchmarked against responses to the National Survey of Children’s Health, (children) [59] and the CDC Adverse Childhood Experiences data (adults) [103, 104], using items included for this purpose.

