### Sample

Data are being gathered from two siblings and up to two parents in 712 families where children will be aged 11 to 16 at the launch of data collection and living in the continental United States, at least half time with their military parent since the deployment. Children each will have experienced the same parental wartime deployment lasting at least 90 days, prior to age 6 for at least one child. A spouse or partner presently living with the military parent will also be invited to participate; an average of 1.66 parents per family is anticipated. Over 1 million service member parents have been deployed to Iraq and Afghanistan since 2001; 33.5% of their children are in the targeted age range [5, 42], yielding an estimated maximum pool of more than 200,000 families after accounting for families with only one child.

Families are not being excluded by divorce so long as the participating children have lived at least half time with the military parent. Families will be excluded if there is an active ongoing investigation for family violence; if any of the prospective participants has a significant cognitive impairment that would prevent comprehending or responding to questions; if the military parent is deployed during the study period; if only one adolescent is willing to participate; or if the military parent does not fit within a stratum with unfilled spaces.

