The sampling frame was constructed using probability methods from DoD personnel records by the Defense Manpower Data Center (DMDC) using information about family members in the Defense Enrollment Eligibility Reporting System (DEERS) and deployments in the Contingency Tracking System (CTS) and PERSTEMPO file. The sample was drawn to ensure representation of service branches, components (active or reserve), and paygrades (officer/enlisted) using a systematic sampling method. To compensate for their low representation in the military [43], female military parents were oversampled to comprise 65% of the sample using explicit stratification [42]. The sample also was stratified according to military parents’ exposure to adverse experiences, compensating for higher nonresponse typical of high risk groups. Based on national data, approximately half the military parents are expected to have experienced at least one of 12 adverse experiences prior to deployment [9]. Based on screening, each family is assigned to gender and risk groups as they enter the study. Interviewers are blind to participant risk group.

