### Sample size determination with statistical power calculation

Data will be obtained from 712 families at baseline, with 2 children and up to 2 parents per family (given divorce rates, 1.66 parents per family are estimated). Stratification will be used to over-select female service members and high-risk families such that 456 families will have female military parents and 356 families will be high risk. Power is calculated for three types of analytic samples:

A baseline/cross-sectional analysis sample of 712 families and 1,424 children (2 per family), and 1,182 parents (1.66 per family);A panel analysis sample composed of families who participate at both waves of the study. Based on experience and other military studies [44], 75% retention is projected, resulting in 534 families, 1,068 children, and 887 parents at Wave 2;A repeated measures sample, comprising all observations from both waves. With a 75% family retention rate, the sample will include 1,246 (= 712 + 534) repeated family observations and 2,670 repeated child observations, and 2,216 repeated parent observations. The repeated measures sample will be the priority sample for testing study hypotheses.

Effective sample sizes are calculated for a two-level, mixed-effects model per Snijders [45] using an estimated within-family ICC = 0.30. Power is estimated for a standardized regression coefficient in a model with 5 covariates and alpha = 0.05. Effect sizes detectable at .80 power are listed in Table 1.

**Table 1 pone.0295007.t001:** Detectable effect sizes.

Direct, Moderation, and Mediation Effects (n = cross-sectional / panel / repeated)	Detectible Standardized Beta		
	Cross- sectional	Panel	Repeated Measures
**1. Family level predictors** (n = 712 / 534 / 1246; effective n = 1095 / 822 / 1917)	0.085	0.098	0.064
**2. Child level predictors** (n = 1424 / 1068 / 2492; effective n = 2034 / 1526 / 3560)	0.063	0.072	0.047

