This study will identify downstream consequences of early exposure to parental deployment during a key developmental period and contribute to literature about children’s risk and resilience in the family context. It will generate insights about how military-connected children compare to national samples of children on key outcome variables, taking exposures to adversity into account. It will contribute to understanding the extent to which military-connected children’s outcomes during adolescence are accounted for by characteristics of parental deployments they experienced early in life vs. their own and their parents’ early exposures to other adverse experiences. It will reveal within-family variations in military children’s outcomes and their antecedants. It will identify which risk and resilience processes appear to be most important for particular adolescent outcomes among children exposed early in life to parental military deployments, and how these effects differ as a function of parent and child assigned sex.

The implications will be important for prevention programs in DoD, schools, health care providers, and community organizations as they consider how best to optimize long-term outcomes for children.

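### The adult comparison with CDC adversity data would largely reflect the enrolment quota on military parents' adversity unless it is weighted using screening counts

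*Protocol article*

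**What the plan says.** **The benchmark.** The Benchmarking section of the protocol article says, by way of example, that "exposures to adverse experiences will be benchmarked against responses to the National Survey of Children’s Health" for children; the same sentence names CDC Adverse Childhood Experiences data for adults. Participants are to be matched on education, minority status, age and sex as far as this can be done. Neither weights nor the risk group is mentioned there.

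**The quota.** The Sample section says: "The sample also was stratified according to military parents’ exposure to adverse experiences". It adds: "Based on screening, each family is assigned to gender and risk groups as they enter the study". A family is excluded "if the military parent does not fit within a stratum with unfilled spaces". The Parent screening section describes the adversity screen as one overall answer on eight kinds of event before military service, and checks that the family's risk group still has room. The sample size section says "Stratification will be used to over-select female service members and high-risk families", sets the total ("Data will be obtained from 712 families at baseline") and fixes the risk split: "356 families will be high risk".

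**The weights.** Weighted estimation that corrects for selection and nonresponse by stratum appears under Model building and estimation, which serves the aim models. Analyses of aims and Innovation also refer to weighting or to correction for unequal selection, again in connection with modelling.

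**The claim.** The Innovation section expects to learn "how military-connected children compare to national samples of children on key outcome variables", and the sentence goes on to say that exposure to adversity will be allowed for.

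**The concern.** The study has no civilian group, so the external benchmarks are its only non-military reference. For military parents, the share with any screened adversity is not something the sample can reveal: enrolment stops in each risk group at a preset number. Matching on demographic variables leaves that split untouched. A statement that military parents report more, less or the same adversity as adults in the CDC data would then mostly restate a recruitment target.

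Weights could undo this, but a weight for the risk group needs the population share of high-risk military parents. The frame is described as drawn from DEERS, CTS and PERSTEMPO, and none of these is described as holding adversity data; risk is learned at screening. The only share in the article is the expectation, taken from national data, that about half of military parents have had at least one adverse experience. Weighting to that figure and then comparing with national data would be circular. It also describes a different variable: twelve experiences before deployment, against eight before joining the military in the screen.

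**Working it through.** **Inputs.** Families 712 and high-risk families 356 (sample size section). Parents 1,182 (same section). The true share *p* of military parents with any screened adversity is not given, so I assume 0.3 to 0.7. The gap *c1 − c0* in a child prevalence between high-risk and low-risk families is not given, so I assume 0 to 0.3. High risk is read as a positive answer to the screen.

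**The plan's own figure.** 356/712 = 50.0%, which agrees with the article's expectation of about half.

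**Military parents, unweighted.** Everyone in the high-risk stratum is positive and no one in the other is, so the sample share is 0.5 × 1 + 0.5 × 0 = 0.50 for every *p*. The bias is 0.50 − *p*.

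**Military parents, weighted.** With weights *w1* = *p*/0.5 and *w0* = (1 − *p*)/0.5, the share is 0.5*w1*/(0.5*w1* + 0.5*w0*) = *p*. The Kish design effect is 0.5(*w1*² + *w0*²) = 2[*p*² + (1 − *p*)²]. For example, at *p* = 0.3 it is 2(0.09 + 0.49) = 1.16, and 712/1.16 = 614.

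| True share *p* | Unweighted | Bias | Weighted | Design effect | Effective families |
|---|---|---|---|---|---|
| 0.3 | 0.50 | +0.20 | 0.30 | 1.16 | 614 |
| 0.4 | 0.50 | +0.10 | 0.40 | 1.04 | 685 |
| 0.5 | 0.50 | 0 | 0.50 | 1.00 | 712 |
| 0.6 | 0.50 | −0.10 | 0.60 | 1.04 | 685 |
| 0.7 | 0.50 | −0.20 | 0.70 | 1.16 | 614 |

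As a yardstick, the nominal standard error of a 50% share in 712 people is √(0.25/712) = 1.9 points, so an interval that ignores the quota would not show a bias of 10 points. The design effect covers the risk weight alone; weights for parent sex and nonresponse would add to it.

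**Single events.** If a fraction *q* of high-risk parents report a given screened event, the sample shows 0.5*q* where the population value is *pq*. At *p* = 0.3 and *q* = 0.5 that is 0.25 against 0.15.

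**All parents pooled.** 1,182 − 712 = 470 parents are not the stratified parent. If their adversity is unrelated to the quota (assumed), the bias shrinks by 712/1,182 = 0.60: 10 points become 6, and 20 become 12.

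**Children.** Child adversity is a separate measure, so the bias is (0.5 − *p*)(*c1 − c0*). It is 0 if child and parent adversity are unrelated, at most 0.1 × 0.3 = 0.03 for *p* from 0.4 to 0.6, and at most 0.2 × 0.3 = 0.06 for *p* from 0.3 to 0.7.

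**The case against.** The strongest reply is that weighting is already promised, that the Benchmarking section is a short illustration, and that a condensed article may leave the building of weights to the full protocol or analysis plan. Nothing says that benchmarks will be unweighted. This stands as a limit on the point: the full documents may settle it. It does not remove the point, because the one adjustment the article does name for benchmarking cannot undo the quota, and a valid risk weight depends on screening counts that must be kept while families are being screened.

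Other parts of the reply also stand:

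- A reader might infer that the child comparison returns the quota too. The documents do not support that. The quota is on the military parent's adversity, child adversity is measured separately, and the effect is indirect.
- The quota fixes one yes/no answer for one parent per family. It does not fix the number or type of events among high-risk parents, or the spouse's adversity. Adult adversity is also asked in detail at interview, so the interview share follows the quota only as far as the two measures agree.
- A reader might infer that the study cannot show how military families compare. That is too strong: valid stratum weights recover the true share. The stated aim for children's outcomes also allows for exposure to adversity.
- If the expected half is right, the bias is close to zero.

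On the last of these, the article is not clear. It speaks of over-selecting high-risk families at a level equal to the share it expects. If this is over-selection relative to the population, *p* is below 0.5 and the unweighted share is too high. The Sample section offers another reason, compensation for higher nonresponse in high-risk groups, but that too leaves the true share to be established.

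**Conclusion.** The point holds for the adult comparison. Unweighted, the military parents' any-adversity share is set at about 50% by enrolment, and the matching named in the Benchmarking section does not change that. The size depends on a true share that the documents do not establish: no bias at 0.5, 10 points at 0.4 or 0.6, and 20 points at 0.3 or 0.7. The child comparison with the National Survey of Children's Health is affected only through the link between child and parental adversity, by about 0 to 6 points under the assumed ranges. Benchmarking is outside the three aims, whose within-sample associations this point does not touch. It is a cheap improvement, not a flaw that defeats the study.

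**What to change.** 1. Keep the yes/no adversity screening result, by parent sex, for every screened military parent, including those turned away because a stratum is full.
2. Estimate the risk-group shares from these counts, not from the assumed national half.
3. State in the Benchmarking section that comparisons use weights combining frame selection by sex, screened risk shares and nonresponse.
4. Set no unweighted adult any-adversity prevalence against the CDC data.

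**Cost.** The question is already asked, so the work is a tally and a weighting step. Intervals widen slightly: the design effect from the risk weight is about 1.00 to 1.16 for assumed true shares of 0.3 to 0.7, that is, 712 families act like 614 to 712. One limit remains: the counts describe families who came forward for screening, and the frame as described has no adversity data with which to correct for those who did not.

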### Analyses of aims

Study aims will be evaluated using structural equation modeling with latent variables (SEM) [105, 106]. The SEM framework is flexible, allowing for: 1) simultaneous estimation of multiple equations (i.e., multiple mediators and final outcomes); 2) mixed-effects modeling approaches to nesting of repeated measures within persons and persons within families; 3) use of latent variables to measure constructs independent of random measurement error; 4) estimation appropriate for the complex sample features, including sampling weights and stratified variance estimation [107]; 5) generalized linear modeling capabilities for outcomes with different distributions such as Poisson, binomial, and categorical outcomes [108–111]; and 6) model fit assessment using statistics and indices.

### Model building and estimation

Measurement models will be developed first, per the psychometric analyses. Latent variables will be used when computationally possible. Structural models will be built in stages paralleling study aims, assessing model fit to the data at each stage [112]. Analyses will be conducted using AMOS, Mplus 7 [111], STATA [113], and SAS [114]. Item-missing data will be handled using Full Information Maximum Likelihood (FIML) procedures available within Mplus and STATA [115]^.^ This approach is advantageous, as simulation studies have found it performs superior to listwise deletion and multiple imputation [116]. Sampling weighted estimation that corrects for unequal selection and non-response across strata will be used [107, 117]. In general, an alpha of 0.05 will be used to determine support or lack thereof for hypotheses. However, focus will be on effect size and confidence intervals for the distribution of effects [118].

A mixed-effects modeling approach to the multilevel, nested data structure will be used to explicitly estimate within- and between-family variability [119]. Change in children’s outcomes will be evaluated with two types of models: 1) Three-level mixed-effect models with time nested within child and siblings nested within families, where change is assessed using a predictor variable indicating baseline and follow-up time points, and interactions with the time variable test the effects of predictors on changes in outcomes; and 2) Two-level models with siblings nested in families that include autoregressive effects for each outcome (i.e., control for Time 1 levels), thus controlling for stable levels of each construct and testing effects on residualized change. Both approaches to modeling change provide rigorous inferences about the hypothesized relationships [120]. Models will control for: 1) parents’ age, education, and minority and employment status; 2) family type and size; 3) military branch and paygrade. Sensitivity analyses will be conducted to ensure that these controls do not obscure important findings. Strategies for analyzing each aim are described below.

#### Analyses for aim 1: To assess direct relationships between the timing, frequency, duration and content of siblings’ early exposures to parental deployments and later youth adjustment

Maladjustment is hypothesized to be greater for children whose exposures began earlier (operationalized as child age at first deployment, including gestational age, coded from archival data), were more frequent (i.e., total number of deployments during the child’s lifetime) prolonged (i.e., total days deployed), ended more recently (i.e., days since end of most recent deployment), or who were exposed to deployments where parents’ experiences were more traumatic (i.e., total scores on self-report Combat Exposure items). These hypotheses will be tested using a SEM framework, where a series of path models will estimate the direct effects of deployment characteristics on each indicator of adjustment. Paths from the independent variables will be tested concurrently, thus establishing the unique association for each deployment risk factor. Interactions between different deployment components—frequency, duration, timing, and content—will also be examined to determine whether long-term effects of deployment are exacerbated or mitigated for various deployment combinations. Within-family comparisons will be conducted to determine whether these direct effects differ across siblings.

#### Analyses for aim 2: To assess the role of parents’ psychological health and family processes in mediating relationships between siblings’ early exposures to parental deployment and later youth adjustment

This aim highlights four indirect pathways through which deployment(s) influence youth adjustment. Deployment factors studied in Aim 1 are expected to be negatively related to parents’ psychological health, parental efficacy, marital relationship quality, and family functioning at Time 1, which in turn will be positively related with youth adjustment at Time 2. The magnitude and statistical significance of the indirect effects of deployment through each of these processes will be tested using the INDIRECT command within Mplus, which employs a product of coefficients method of testing mediation [121] and the bootstrap method to compute standard errors for the significance test [122]. Importantly, the four indirect pathways will be tested concurrently, highlighting not only which pathways are critical for understanding the potential enduring effects of parental deployments on youth adjustment, but also the relationships among them. Differences across siblings also will be assessed.

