### Aim 3: To assess the moderating role of parent and sibling sex, and vulnerability and support in the relationship between siblings’ early exposures to parental deployment and later youth adjustment

Relationships between parental deployments and youth adjustment are expected to be stronger in the presence of greater vulnerability (i.e., adverse experiences, mental health problems) and less support (i.e., availability and use of formal and informal support) prior to and following deployment. Parent and youth sex will be examined as potential moderators of the impact of the relationship between exposure to parental wartime deployment and outcomes.

Existing studies of military children are limited by significant design constraints, such as focusing only on current or recent deployments, which leaves unanswered questions about long-term consequences [10]. Few studies have included data about military parents’ experiences before deployment, which may lead researchers to attribute to deployments parental factors that not only existed before, but may have conditioned parents’ reactions to deployment. Most studies have relied almost completely on parents’ reports for data about children, which can be influenced by parents’ own symptoms [41]. Few studies have compared the consequences of mothers’ and fathers’ deployments, none in the long term. The proposed study is unique because its combination of archival and new data surmounts these design constraints of existing studies.

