**4. Family Functioning.**			
***a. Overall*:**	Family Assessment Device (General Functioning) (α = .92); [80]	Survey	Survey
***b. Parent child relationship*:**	Items from the National Survey of Children’s Health [81]	Survey	
***c. Sibling relationship*:**	Network of Relationships Inventory (24; α>.70) [82]		Survey

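### Aim 2 compares same-reporter with cross-reporter mediation paths without a safeguard, so where deployment is related to a mediator the comparison of pathways tilts toward the same-reporter ones

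*Protocol article*

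**What the plan says.** The analysis section for Aim 2 expects deployment to be negatively related to four mediators at Time 1, including "family functioning at Time 1, which in turn will be positively related with youth adjustment at Time 2". The estimator "employs a product of coefficients method of testing mediation [121] and the bootstrap method to compute standard errors". The purpose of testing the pathways jointly is stated: "the four indirect pathways will be tested concurrently, highlighting not only which pathways are critical for understanding the potential enduring effects".

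Table 2 fixes who reports what:

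- **Sibling relationship** ("Network of Relationships Inventory (24; α>.70"), **monitoring** and **differential treatment**: youth only.
- **Parenting acceptance/rejection** and the **Family Assessment Device**: parent and youth.
- **Coparenting** and **parent-child relationship items**: parent only.
- **Couple relationship**: parent only.
- **Parents' mental health**: parent or medical records, apart from a spirituality scale that youth also answer.
- **Social-emotional outcomes**: youth only throughout.
- **Other outcomes**: risky behavior, substance use, coping and academic engagement are youth only. The Strengths and Difficulties Questionnaire (SDQ) has both reporters. Flourishing and school problems are parent only. Health care utilization comes from records.
- **Exposure**: deployment records, plus combat exposure from parent interview.

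The text closing the Aim 3 statement faults earlier work: "Most studies have relied almost completely on parents’ reports for data about children, which can be influenced by parents’ own symptoms". Under Analyses of aims, latent variables are credited with removing random measurement error. Under Model building and estimation, one of the two change models controls the Time 1 outcome.

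**The concern.** Some of the paths being compared have the same person describing both mediator and outcome; others do not. A youth who tends to answer negatively will rate the sibling relationship, parental monitoring and their own mood lower, at both waves, whether or not one affects the other. That raises the mediator-to-outcome coefficient for youth-youth pairs and leaves parent-youth pairs untouched. For parent-reported outcomes the tilt runs the other way.

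The plan's stated safeguards do not remove this. Latent variables built from one reporter's scales absorb a shared style instead of removing it. A 12-month lag does not remove a stable style. The data-cleaning section adds a variable as a control when it is found to introduce bias, but reporter does not vary within a youth-only measure and cannot enter as a covariate. The Time 1 control shrinks the spurious path without eliminating it, and the Aim 2 text does not say which change model it uses.

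At stake is the statement about which pathways are critical. The sibling pathway, singled out for particular attention in the Aim 2 statement, rests on one listed instrument from one type of reporter.

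**Working it through.** **Scale, from the plan.** Table 1 gives a detectable standardized beta at 80% power in the panel sample (534 families, 1,068 children, ICC 0.30). With (1.960 + 0.842) / √(effective n):

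- family-level: 2 × 534 / 1.3 = 821.5, beta 0.098 (stated 0.098);
- child-level: 1,068 / 0.7 = 1,525.7, beta 0.072 (stated 0.072).

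Table 1 is not in error here; it shows how small a path the study can declare significant.

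**Assumptions not in the documents.** Reporting style makes up a share *v* of the variance of mediator and outcome, with *v* from 0.10 to 0.30. The outcome's true-score stability ρ is 0.5 to 0.7. There is no true mediator-outcome link.

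**Step 1: spurious mediator-to-outcome path (b).** Without the Time 1 outcome, b = *v*. With it, the Time 1–Time 2 correlation is r = (1 − *v*)ρ + *v*, and b = *v*(1 − r)/(1 − *v*²), which reduces to *v*(1 − ρ)/(1 + *v*).

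| *v* | b, no control | b, controlled, ρ = 0.5 | ρ = 0.6 | ρ = 0.7 |
|---|---|---|---|---|
| 0.10 | 0.10 | 0.045 | 0.036 | 0.027 |
| 0.20 | 0.20 | 0.083 | 0.067 | 0.050 |
| 0.30 | 0.30 | 0.115 | 0.092 | 0.069 |

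For example, *v* = 0.20 and ρ = 0.6 give 0.20 × 0.4 / 1.2 = 0.067. The control cuts the path by more than half but leaves it close to the detectable 0.072.

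**Step 2: the indirect effect, which is what Aim 2 tests.** The product a × b also needs a deployment-to-mediator path *a*. Simulation settings: n = 822 (1,068 / 1.3), ρ = 0.6, one youth-reported and one parent-reported mediator tested together on a youth-reported outcome, true b = 0, and a Monte Carlo product interval in place of the bootstrap. There were 1,500 to 4,000 replicates per cell; ranges show the spread between runs. Table 1's larger child-level effective n of 1,526 would raise the rates where *a* is not zero.

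False-mediation rate for the youth-reported mediator:

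| Condition | *v* = 0.10, no control | *v* = 0.10, controlled | *v* = 0.20, no control | *v* = 0.20, controlled |
|---|---|---|---|---|
| a = 0, reporting unrelated to deployment | 3–4% | 1% | 6% | 3% |
| a = 0.10 | 60–61% | 19–20% | 73–74% | 49–51% |
| a = 0.18 | 82–84% | 27–29% | about 100% | 72–74% |
| a = 0, deployment shifts youth reporting (r = 0.2) | 33–34% | 9–10% | 73–75% | 46–48% |

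At a = 0.18 the parent-reported mediator is declared significant 5–6% of the time. The value 0.18 is borrowed from the low end of the 0.18 to 0.32 range in the power section; that range concerns deployment effects on youth outcomes, so its use for *a* is an assumption.

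**Step 3: ranking of two equally strong true mediators** (a = 0.18, b = 0.10). With no reporter share, both indirect effects are 0.018 without the Time 1 control.

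| *v* | Control | Youth-reported | Parent-reported | Ratio |
|---|---|---|---|---|
| 0.10 | no | 0.033 | 0.016 | about 2 |
| 0.10 | yes | 0.012 | 0.005 | about 2 |
| 0.20 | no | 0.046 | 0.013 | about 3.5 |
| 0.20 | yes | 0.016 | 0.004 | about 4 |

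**The case against.** **Reporter bias does not manufacture mediation.** A reader might infer that a shared reporter is enough to produce it. The documents do not support that. No exposure is youth-reported, so the bias enters only b; with *a* at zero and reporting unaffected by deployment, false mediation is 1% to 6%. A rejection rate for b alone must not be read as a false-mediation rate. This stands and limits the point. But Aim 2 itself hypothesises a non-zero *a*, so the harmful condition is the one the study expects.

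**The pathways are not purely single-reporter.** Parenting quality and the Family Assessment Device have both reporters, coparenting is parent-reported, and parental diagnoses and child health care use come from records. This stands too. The strong form applies to three mediators (sibling relationship, monitoring, differential treatment); elsewhere multiple informants dilute it.

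**The plan does not simply repeat the fault it criticises.** That is another tempting inference. The criticism concerns parents' reports about children, and youth self-report answers it. It returns only where parents' symptom scales meet parent-reported outcomes.

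**A condensed article may leave informants and method factors to the analysis plan.** That is fair for modelling detail. Here the reporter allocation and the conclusion to be drawn from the joint test are both on the page, and together they give an uneven comparison.

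**Requiring a different reporter for every path is not feasible.** Couple and parent-symptom scales have no youth version, families average 1.66 parents, and monitoring and differential treatment are perceptions by design. This stands, which is why a sensitivity analysis is the right remedy.

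**Conclusion.** The point holds in limited form. As written, Aim 2 compares same-reporter with cross-reporter paths and draws conclusions about their importance, with no stated protection against shared reporting style. That style can inflate an indirect effect, and shift the ranking, where deployment is related to the mediator or to how youth report; it does not generate mediation on its own.

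At a = 0.18 and a 10% to 20% reporter share, false mediation is roughly 83% to 100% without the Time 1 control and 27% to 74% with it. Equally strong mediators differ about two- to fourfold by reporter. The reporter share, *a* and outcome stability are assumptions with no anchor in the documents, and the model is a simplified two-mediator version of the planned analysis. The direction does not depend on the exact values; the size does. The data stay usable. What needs protection is the claim about which pathway is critical.

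**What to change.** Add to the Aim 2 analysis section a pre-specified cross-reporter sensitivity analysis, and state that no pathway will be called critical unless its result is consistent there.

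- **Youth-reported outcomes:** use the co-sibling's Network of Relationships report for the target child, and the parents' acceptance/rejection and Family Assessment Device reports. The co-sibling option assumes each youth rates the participating sibling, which Table 2 does not say and should be confirmed.
- **SDQ:** use the version from the reporter who did not supply the mediator.
- **Model:** use the Time 1 outcome-controlled model for this comparison.
- **Single-reporter mediators** (monitoring, differential treatment): keep the path, label it same-reporter and leave it out of the ranking. Treat parent symptom or couple scales set against flourishing or school problems in the same way, unless different parents supplied the two reports.

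The cost is analysis wording; the reports are already planned, and both siblings must take part for a family to be eligible. The downside is weaker cross-reporter associations and hence some loss of precision. The text should be settled before outcome data are analysed.
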